**Methods and analysis:**

A total of 1000 pregnant people currently suffering from, or at risk of, antenatal depression will be recruited across six countries. All participants will be between 13 and 28 weeks’ gestation and will be given access to the new purposefully developed HappyMums mobile application, to use from enrolment until 2 months postpartum. The application leverages passively collected data from smartphone sensors relating to physical activity and behaviour, as well as requiring active engagement from the user to complete mental health questionnaires and ‘game-like’ activities. Digital data types will be combined with traditional mental health measurement methods, such as standardised questionnaires and interviews, to develop novel predictive models capable of identifying mental health trajectories in women at risk of developing antenatal depression and to test the app’s utility for use as personalised risk prediction and depression identification tool. The primary outcome of this study is to determine what proportion of users will continue to use the mobile application and engage with its tasks and activities at least weekly, while secondary exploratory outcomes include assessing usability of the app and testing the predictive ability of a novel machine learning-based model. These outcomes will, for the first time, be assessed by integrating active as well as passive data.

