### Participants

Participants for this study will be n=1000 pregnant people (approximately 150 per centre), who are either currently suffering with AD symptoms, or meet the criteria for at least one risk factor for AD, as determined by the expertise of the consortium, literature searches and the current availability of screening questionnaires. Eligibility will be determined using a screening questionnaire specifically created within the consortium, as shown in online supplemental material.

Inclusion criteria: pregnant participants, aged 18 or older, enrolled from 13 to 28 weeks’ gestation and scoring >0 on the screening instrument. Participants must have a satisfactory understanding of the national language of their recruitment site, in order to provide fully informed consent. They must also own a smartphone capable of downloading and running the HappyMums application, which will be available in all national languages.

Exclusion criteria: Inability to give informed consent.

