### Data analyses

Given the multinational nature of the study, data analyses will be conducted at site-specific and study-wide levels. To address the aim of testing the usage of the app in the at-risk pregnant population, sites will specifically examine their usage data at a site-specific level, before being appraised study-wide. This will be conducted first by developing a set of descriptive analyses to address the primary objective by profiling the proportion of participants who engaged weekly with the mobile application and examining demographic and psychosocial characteristics of active and non-active users, including the antenatal trajectories of depressive symptoms as measured by the EPDS.

Following data completion, study data from all sites will be integrated within a secure federated learning framework to train and evaluate predictive models for maternal depression. This decentralised approach enables sensitive data to remain at local sites while allowing cross-site model training, preserving participant privacy and ensuring diversity in the learnt patterns. Predictive modelling will focus on classifying the risk of AD, as measured by EPDS (Edinburgh Postnatal Depression Scale) scores at baseline, third trimester and postpartum follow-up, with key outcomes defined as binary variables (eg, EPDS ≥13) and continuous trajectories of depressive symptoms over time.

Three supervised machine learning models will be evaluated: Random Forest, Support Vector Machines and logistic regression. These models will be trained on a combination of app-derived and traditional data sources. Input features will be grouped into distinct domains: (1) passive smartphone-derived data (eg, mobility patterns, phone usage, sleep-wake cycles); (2) active self-report data (eg, mood ratings, cognitive performance from app-based tasks); (3) psychosocial and clinical history data (eg, social support, previous mental health diagnoses, adverse life events); and (4) demographic and obstetrical information (eg, age, parity, gestational age, education level).

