Model performance will be evaluated using cross-validation techniques within the federated environment. Feature importance will be assessed using internal metrics (eg, Gini importance in Random Forests), and model-agnostic interpretability will be explored via SHAP (SHapley Additive exPlanations) analysis. This will help identify the most influential individual predictors and feature groups contributing to AD risk, aiding interpretability and translational relevance for clinical stakeholders. In doing so, the study aims to provide interpretable, generalisable and privacy-preserving models for early identification and personalised risk assessment of maternal depression.

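### Pooled EPDS ≥13 accuracy in a cohort mixing current cases with women only at risk cannot, on its own, support the early-identification claim

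*Protocol article*

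**What the plan says.** **Who is enrolled.** The Participants section takes pregnant people "who are either currently suffering with AD symptoms, or meet the criteria for at least one risk factor for AD". They must be "enrolled from 13 to 28 weeks’ gestation and scoring >0 on the screening instrument", and the list of exclusions is one line: "Exclusion criteria: Inability to give informed consent". The Abstract describes the same mixed group: "A total of 1000 pregnant people currently suffering from, or at risk of, antenatal depression will be recruited across six countries". Women already above an EPDS threshold are therefore in the cohort by design.

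**What is modelled.** Under Data analyses, "Predictive modelling will focus on classifying the risk of AD, as measured by EPDS" at three times (baseline, third trimester and postpartum follow-up), "with key outcomes defined as binary variables (eg, EPDS ≥13) and continuous trajectories of depressive symptoms over time". Inputs include passive phone data, mood ratings, cognitive tasks, and psychosocial and obstetric history. No restriction to, stratification by, or separate performance for women below the threshold at entry is stated.

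**When baseline is measured.** Table 1 has researchers collect EPDS from every participant at enrolment. The Recruitment process section puts the initial assessment before app access.

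**What is claimed.** The Abstract speaks of models for "identifying mental health trajectories in women at risk of developing antenatal depression", and Data analyses ends with "privacy-preserving models for early identification and personalised risk assessment of maternal depression". The Abstract also names identification of depression as a use of the app, and the Introduction names identifying depression and response to treatment as things the models will be tested for.

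**The concern.** A woman at EPDS ≥13 on entry who is still there in the third trimester shows persistence. A woman below 13 on entry who later reaches it shows onset. Both count as positives for the same later outcome, but only the second bears on whether the app can flag women who are going to develop depression.

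The baseline outcome is clearer still. It is fixed before any app data exist, so app-derived features can at best recognise a state already present.

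If one pooled figure is reported, a digital marker that merely tracks how unwell a woman was at enrolment could be read as an early-warning signal. The Gini and SHAP rankings, which are meant to inform clinical stakeholders, could not be attributed to onset rather than to existing illness.

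**Working it through.** The article gives no expected EPDS distribution, persistence, AUC or accuracy, so there is no stated figure to reproduce. The check has a part that needs no assumptions and an illustration that does.

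**1. Baseline outcome (no assumptions).** The initial assessment comes before app access. Every woman positive on baseline EPDS is therefore an existing case: 100% by definition.

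**2. Later outcomes (assumed inputs).** Write B for EPDS ≥13 at entry and L for EPDS ≥13 later.
- Share of later cases already present = P(B and L) / P(L).
- Onset cases per 1000 = 1000 × P(not B and L).
- AUC of a marker for L, computed in all women and again among women not in B.

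Assumptions, none of them in the article: EPDS normal with SD 5.5, rounded and limited to 0-30; mean 8, 10 or 12 at both times; correlation between entry and later score 0.5, 0.6 or 0.7; 400,000 simulated women in each of the nine scenarios. With rounding, P(B) = P(Z ≥ (12.5 − mean)/5.5), which is about 21%, 32% and 46% for the three means.

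| Quantity | All women | Women <13 at entry |
|---|---|---|
| Share of later cases already ≥13 at entry | 44-73% | – |
| AUC, marker correlating 0.7 with entry state, no other information | 0.66-0.74 | 0.57-0.66 |
| Same marker, mean 10, correlation 0.6 | 0.70 | 0.61 |
| AUC, marker correlating 0.6 with later state | 0.78-0.80 | 0.75-0.80 |
| Onset cases per 1000 | about 90-165 | – |

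Against the *baseline* outcome, the entry-state marker scores 0.83-0.85.

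**3. Wider ranges.** A second simulation let the share ≥13 run from 15% to 65%. That range is the Introduction's general prevalence of antenatal depression, borrowed as a range and not a forecast for this cohort. The correlation ran from 0.4 to 0.8.
- Already present: 32-85% of later cases.
- Entry-state marker: AUC 0.63-0.79 in all women, 0.54-0.70 in women below the threshold at entry.
- Baseline EPDS ≥13 yes/no as the sole predictor: 0.60-0.80 in all women, and 0.50 by definition below the threshold.
- Onset cases: 59-185 per 1000.

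**4. Hand check of one cell.** With 50% above threshold at both times and correlation 0.6, the share already present is 1/2 + arcsin(0.6)/π = 0.5 + 0.6435/3.1416 = 0.705, against a simulated 0.70. Onset per 1000 = 500 × (1 − 0.705) = 148, as simulated.

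**The case against.** **Recognising current cases is a declared aim.** True. Baseline EPDS is itself a listed outcome, the Abstract and Introduction name identification of depression, and studying response to treatment needs women who are already ill. Early identification could also mean finding an unrecognised existing case sooner. So the pooled result is not meaningless. It still cannot carry a statement about women at risk of developing depression.

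**Silence is not pooling.** The article does not say that entry state will be ignored, ≥13 is only an example, and continuous trajectories can distinguish rising, persistent and remitting courses. A condensed article may leave stratified reporting to a fuller document. This has weight, but the point rests on what is stated: one mixed population, three outcome times including baseline, and an onset-type claim. The problem arises at any cut-off, and no conditioning on entry level is stated for the trajectories either.

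**The loss of AUC is built in.** For the entry-state marker it is, because that marker is defined to know nothing else. A marker of later state barely changes, and one tracking only change since entry did better below the threshold (0.72-0.74) than pooled (0.66-0.71). Inflation is therefore possible, not inevitable.

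**A stronger reading to resist.** A reader might infer that pooled accuracy will mostly reflect existing cases, or that the top-ranked predictors will be correlates of illness at enrolment. For the later outcomes the documents support neither. The share already present can be a minority (44% at the low end of the main scenarios, 32% in the wider ranges), and no feature ranking was simulated.

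**Conclusion.** The point holds in limited form. As written, the plan does not separate onset from persistence, and one of its three outcome times contains existing cases only. Pooled accuracy is valid for case recognition; what it does not support on its own is the early-identification conclusion.

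The direction of the risk is clear, but its size is not. It depends on the share of women ≥13 at entry, on how persistent scores are, and on whether the markers track entry state or later state. The article gives none of these, so the figures above are illustrations under assumed inputs.

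Prediction is a secondary, exploratory aim. The primary outcome, weekly engagement with the app, is not affected.

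**What to change.** Keep the pooled result and label it as recognition of cases. In addition, use the baseline EPDS already in Table 1 to report third-trimester and postpartum performance, and the feature rankings, separately for:

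1. women below the threshold at entry: later score at or above it (onset);
2. women at or above it at entry: persistence versus remission.

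Use only predictors collected before the outcome in question. Base the early-identification conclusion on (1), and state this before modelling starts so that the more flattering figure cannot be chosen afterwards.

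This changes analysis wording only and needs no new data. The costs are:
- a smaller sample for onset: about 90-165 cases per 1000 under the main assumptions;
- noise from scores near the cut-off, since a move from 12 to 13 would count as onset;
- a split that is not identical to the enrolment distinction, because eligibility rests on the consortium's screening questionnaire, not on EPDS;
- probably a lower headline accuracy.

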### Aims

To test the new HappyMums app, which will include smartphone-based questionnaires, passive data collection, game-style emotional recognition and cognitive tests and psychoeducational material.To determine whether pregnant people, at risk of, or currently suffering from AD, find it acceptable and feasible to use the ‘HappyMums’ mobile application through trimesters two and three of pregnancy, as a method of passively and actively collecting data which could be used to monitor their mental health during pregnancy.To use the data collected by the mobile application to build models capable of predicting antenatal mental health trajectories, using ‘traditional’ approaches such as standardised questionnaires and interview as comparators.

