#### Secondary objectives

To assess the usability of the application, the ‘Systems Usability Scale’ and ‘Unified Theory of Acceptance and Use of Technology’ questionnaires will be administered to users after they cease their use of the application (after giving birth).To test the predictive ability of the model, using data passively and actively collected by the application, prediction of antenatal mental health trajectories of users as determined by the app will be compared with standardised measures via the Edinburgh Postnatal Depression Scale (EPDS) and the Patient Health Questionnaire 9 item, available for app users to complete every 2 weeks. A separate subanalysis will be conducted in the subsample receiving a comprehensive, face-to-face clinical assessment with the Mini International Neuropsychiatric Interview (MINI) at baseline and in the early postpartum.

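### The objectives test prediction from app-collected data, but every stated model is trained on app and traditional data together, so no stated result gives the app's own accuracy or its added value

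*Protocol article*

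**What the plan says.** All references are to the protocol article.

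- **Aims, third aim.** The models come from app data: "To use the data collected by the mobile application to build models capable of predicting antenatal mental health trajectories". Traditional "approaches such as standardised questionnaires and interview as comparators" complete the aim.
- **Secondary objectives.** The second objective is "To test the predictive ability of the model, using data passively and actively collected by the application". The predicted trajectories "as determined by the app will be compared with standardised measures via the Edinburgh Postnatal Depression Scale (EPDS") and the PHQ-9, with a separate subanalysis against the MINI in the subsample that has it.
- **Abstract, Methods and analysis.** "Digital data types will be combined with traditional mental health measurement methods" in order to develop the predictive models.
- **Data analyses.** Random Forest, Support Vector Machines and logistic regression are named. "These models will be trained on a combination of app-derived and traditional data sources". The inputs fall into four domains: (1) passive smartphone data; (2) active self-report data; (3) psychosocial and clinical history; (4) demographic and obstetrical information. The outcome is the EPDS, as a binary variable (for example, 13 or more) and as a continuous trajectory.
- **Data analyses, interpretation.** Performance is assessed by cross-validation. Gini importance and SHAP are planned as well: "This will help identify the most influential individual predictors and feature groups contributing to AD risk".

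**The concern.** The objective names one set of predictors and the analysis uses a larger one. Table 1 and the Risk factor assessment section show that much of domains 3 and 4 is gathered by researchers: demographics, adult attachment and partner abuse at baseline, and further scales in the opt-in subsample. These items could be had without the app.

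This matters more than usual in this cohort. Under Participants, everyone enrolled has current symptoms or at least one risk factor, and domain 3 includes previous mental health diagnoses. History alone may therefore carry much of the prediction. A good combined result would not show whether weeks of sensing and tasks match, beat or add to what a short history already gives. Yet the Data collection section says the app's main purpose is to explore which data types predict best, and the mobile application section foresees a clinician dashboard of app data. Both call for the performance of app data alone, or their increment.

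**Working it through.** **Step 1. Objective against analysis.**

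| Element | Third aim and secondary objective | Data analyses |
|---|---|---|
| Predictors | Data collected by the app | App-derived plus traditional data, four domains |
| EPDS | Standard against which the app's prediction is compared | Outcome |
| History, demographic and obstetrical data | No role named | Predictors (domains 3 and 4) |
| App-only performance | What is to be tested | Not stated |
| Gain over traditional data | Not named explicitly | Not stated |

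The EPDS row is consistent. The predictor row is not, and the app-only row follows from it.

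**Step 2. Can importance measures fill the gap?** The article gives no AUC, prevalence or effect size and disclaims a power calculation, so there is no figure of its own to reproduce. The check is an illustrative simulation on assumed inputs:

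- one app score A and one traditional score T, both standard normal, with correlation 0, 0.4 or 0.8;
- logit P(Y = 1) = b0 + bA·A + bT·T, with bT = 1.0, bA = 0, 0.3 or 0.6, and b0 set to give a prevalence of 25%;
- 1,000,000 records per setting.

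For a linear model on equally scaled inputs, the app's share of mean absolute (interventional) SHAP is bA / (bA + bT):

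- bA = 0: 0 / 1.0 = 0.00
- bA = 0.3: 0.3 / 1.3 = 0.23
- bA = 0.6: 0.6 / 1.6 = 0.375

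The gain is the combined AUC minus the traditional-only AUC.

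| App SHAP share | Correlation | Combined AUC | App-only AUC | Traditional-only AUC | Gain |
|---|---|---|---|---|---|
| 0.00 | 0 | 0.744 | 0.500 | 0.744 | 0.000 |
| 0.00 | 0.4 | 0.744 | 0.596 | 0.744 | 0.000 |
| 0.00 | 0.8 | 0.743 | 0.694 | 0.743 | 0.000 |
| 0.23 | 0 | 0.751 | 0.572 | 0.740 | 0.011 |
| 0.23 | 0.4 | 0.770 | 0.663 | 0.762 | 0.008 |
| 0.23 | 0.8 | 0.784 | 0.749 | 0.781 | 0.003 |
| 0.375 | 0 | 0.771 | 0.639 | 0.732 | 0.039 |
| 0.375 | 0.4 | 0.800 | 0.721 | 0.773 | 0.027 |
| 0.375 | 0.8 | 0.820 | 0.794 | 0.811 | 0.009 |

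At a fixed non-zero share, app-only accuracy rises with the correlation while the gain falls. One importance figure is therefore compatible with quite different answers to both questions.

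**Step 3. Can the separate models be fitted, and on what inputs?** Yes, because the domains are already distinct. Table 1 does constrain the inputs:

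- Social support (MSPSS) is measured at weeks 25 and 35, in the opt-in subsample only. At the stated minimum of 30 per site that is 7 × 30 = 210 people, against a target of 1000.
- Brief Life Events is listed from birth to 2 months postpartum.
- The app itself collects EPDS, PHQ-9 and GAD-7 every two weeks, and the Manual data entry section classes these as traditional measures. The article does not say whether they belong to domain 2.

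**The case against.** The strongest reply has four parts.

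1. **Comparators may mean reference standards.** The secondary objective compares app-based predictions with EPDS, PHQ-9 and MINI, and EPDS is the model outcome. This is the most natural reading, and it stands. A reader might infer that the aims promise a contest between app data and a rival set of history predictors; the text does not say so. The predictors are still named there as app data, so the mismatch remains.
2. **Combining sources is open design.** The abstract says so, and the end of the Introduction speaks of aggregating data types. That stands too, but it moves the conflict to between these passages and the objectives; it does not remove it.
3. **Some separation is foreseen.** A reader might infer that the app's predictive value cannot be separated out at all. The documents do not support that: domains are distinct, importance by feature group is planned, and nothing in the design prevents single-source models. What is missing from the stated analysis is a performance estimate, which importance measures do not supply (Step 2).
4. **This is detail for an analysis plan.** A full protocol or SAP, neither shown, may specify such models. For metrics and model lists alone that would settle the matter. Here, however, the article fixes the training inputs, and fixes them differently from its own objective.

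A reader might also infer that the study will credit the app with whatever the combined model achieves. The article makes no such claim. It speaks of models for early identification and risk assessment, and calls these outcomes exploratory.

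**Conclusion.** The point holds as a mismatch between objective and analysis. The third aim and the secondary objective test prediction from app data; the stated models use app and traditional data together. Followed as written, the analysis reports combined performance only, and Gini or SHAP by feature group gives neither app-only accuracy nor the gain over traditional data.

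The size cannot be computed from the article. The simulated figures show only that one importance share can accompany very different performance. They rest on two scores, a logistic model, an assumed prevalence of 25% and assumed coefficients and correlations, and they do not forecast this study.

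The plan should be changed on this point, but the flaw is not fatal: the primary outcome on weekly engagement is untouched, and the data to be collected are enough to put it right. If an unseen SAP already contains app-only and traditional-only models, only the wording remains to be reconciled.

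**What to change.** For each outcome, fit three models on the same participants and the same cross-validation folds:

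- (a) traditional only, from domains 3 and 4;
- (b) app only, from domains 1 and 2;
- (c) combined.

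Report discrimination and calibration for each. Use (b) to answer the secondary objective, and (c) minus (a), with an interval, for added value. Keep Gini and SHAP as descriptive.

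Define the inputs by timing and availability:

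- Limit (a) to domain 3 and 4 items available for all participants before the outcome. By Table 1 this leaves out MSPSS for the full cohort, and Brief Life Events for any outcome that precedes it. The screening questionnaire is in a supplement not shown here; if it covers these topics, its items could stand in.
- State whether in-app EPDS, PHQ-9 and GAD-7 are predictors in (b). EPDS is also the outcome, so a model that includes it partly predicts EPDS from EPDS.
- Say how the baseline EPDS outcome is handled. Under Recruitment process, app access follows the initial assessment, so no app data precede it.

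The fallback is to reword the third aim and the secondary objective to describe a combined model. That removes the contradiction but gives up the question about the app.

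The cost is revised wording and extra model runs in the federated environment, with no new data. The app's stated contribution may turn out smaller than a combined result suggests.

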##### Interaction with system

The user will directly interact with the system to provide data which can be interpreted for use in mental health prediction. Users will be given access to cognitive tasks two times during their pregnancy, which have been selected to measure domains known to be impacted by depressive symptoms:^29^ spatial memory, mathematical operations and verbal fluency. They will also complete the Stroop test, to measure negative attentional bias, also known to be associated with depressive symptoms.^30^ In addition, it has been shown that perinatal depression can impact a person’s ability to recognise emotion from facial cues.^31^ Therefore, the application includes two emotion recognition tasks^32^,^36^ in which participants will be shown adult faces from the Vienna Emotion Recognition Task database, and infant faces from the Tromso Infant Faces Database,^37^ and asked to identify the emotion shown on the face, chosen from a list.

In addition to the cognitive and emotion recognition tasks which will be made available at specific time points during gestation, users will have access to a number of activities which they can complete at leisure. These include a ‘How was your day’ activity, where users can make verbal answers, and as an optional extra, make a short video recording of their face. These audio and video recordings will subsequently be used to extract acoustic features of speech and video features related to facial affect and expression.

Users will also have access to a ‘Reflections’ exercise, in which they will be able to type short text answers to miscellaneous questions such as ‘If you could meet any historical figure, who would it be and why?’. The typed keys will be collected by keyboard interaction data, as well as the underlying movement of the phone acquired by accelerometer sensors in the phone.

Moreover, users will have access to a mood and events diary, in which they can keep track of their mood as much as they please and identify factors and events which might have contributed to their current mood. They are also able to answer two sleep questions to monitor their quality and duration of sleep. Both mood and events and the sleep diary will be visualised for the user, to aid with their self-monitoring.

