We acknowledge that there are certain limitations and key risks of this protocol which should be taken into consideration. In terms of data quality and cross-country implementation, we recognise that there is a risk that different languages and cultural contexts could lead to heterogeneity in data collected. To mitigate this, active data collected is in the form of standardised self-report questionnaires which have validated translations. In addition, tasks on the app do not require language input, such as typing speed and voice recognition. Furthermore, researchers on the project have undergone extensive training at all sites to reach reliability in data collection, both online and face-to-face at consortium meetings. As with any study involving the use of technology, we have anticipated technical challenges which could potentially arise, due to different operating systems, phone models and software updates. To mitigate this, the app has been extensively tested by team members at all sites and rounds of feedback have been provided to developers, Ab.acus. The app developers have created in-depth user manuals which will be shared with participants and researchers, to use for troubleshooting, if technical challenges arise. Researchers have trained in guiding participants through any technical errors to ensure smooth usage of the app. As this is a multicentre clinical study, we understand that there might be concern about data sharing and regulations. To mitigate this, a Federated Analysis environment will be developed by the University of Barcelona, whereby models will be trained without data leaving local servers. Furthermore, a Joint Controllership Agreement and Consortium Agreement has been executed by all consortium partners and data collecting sites to ensure ethical use of data. We acknowledge that participants will be completing a battery of self-report measures, which can be burdensome. To mitigate this, a small subgroup, that is, the comprehensive/validation cohort will undergo a more in-depth assessment and will be compensated for their time accordingly. Finally, a current limitation of this methodology is that it excludes individuals who lack access to an appropriate smartphone, who may be part of a deprived demographic group and experience many barriers to care.

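### One safeguard offered against language heterogeneity, that app tasks need no language input, is contradicted by the protocol's own task list, and language-dependent features feed models trained across six countries

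*Protocol article*

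**What the plan says.** The limitations text at the end of Data analyses names the risk openly: "we recognise that there is a risk that different languages and cultural contexts could lead to heterogeneity in data collected". Three mitigations follow. The first is that "active data collected is in the form of standardised self-report questionnaires which have validated translations". The second is "In addition, tasks on the app do not require language input, such as typing speed and voice recognition". The third is training of researchers at all sites.

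Interaction with system describes what the app asks users to do. The cognitive tasks cover "spatial memory, mathematical operations and verbal fluency". In the *How was your day* activity users answer aloud, and acoustic features are later extracted from the recordings. In *Reflections*, "they will be able to type short text answers to miscellaneous questions", and the keys typed are collected. Under Participants, the app is offered in every national language of the recruiting sites.

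Data analyses lists cognitive performance on app tasks within the second group of model inputs. Predictors are to be ranked by Gini importance and SHAP. On validation it says "Model performance will be evaluated using cross-validation techniques within the federated environment", and on purpose, "the study aims to provide interpretable, generalisable and privacy-preserving models".

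**The concern.** A mitigation is useful only if it is true of the data that reach the model. Here it is not. Verbal fluency scores, speech acoustics and keystroke timing all come from producing language, and their distributions may differ between languages for reasons unrelated to mood. The other two mitigations do not fill the gap: validated translations protect questionnaire scores, and researcher training does not act on features that the phone generates.

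The models are trained jointly across seven sites in six countries. If a language-dependent feature differs by country, and the frequency of EPDS ≥13 also differs by country, the feature can gain apparent predictive value by indicating where the participant lives. It could then rank high in the Gini or SHAP output offered to clinicians, and pooled discrimination could be higher than what the model achieves among women in the same country.

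**Working it through.** **Step 1. Set the passages side by side.**

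| Task or activity (Interaction with system) | What is recorded | Needs language production? |
|---|---|---|
| Verbal fluency | Task performance | Yes |
| *How was your day* | Spoken answers, acoustic features | Yes |
| *Reflections* | Typed answers, keyboard data | Yes |
| Spatial memory, mathematical operations | Task performance | Not evidently |
| Emotion recognition | Choice from a list | Not evidently |
| Stroop | Task performance | Cannot tell; stimuli not described |

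The challenged sentence can be read in two ways. If typing and voice are examples of tasks free of language, they are poor examples, since both signals arise from writing or speaking. If they are examples of language input that the tasks do without, *Reflections* and *How was your day* contradict it. Neither reading fits verbal fluency. The first mitigation is also incomplete, because active data include task performance as well as questionnaires.

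**Step 2. Do these data reach the models?** Verbal fluency does, as cognitive performance on an app task. The speech and keyboard features are not named among the model inputs, whose lists are given as examples. However, Interaction with system introduces these interactions as a source of data for mental health prediction.

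**Step 3. How large could the effect be?** The article states no figure to reproduce: there is no power calculation and no prevalence by site. The following is an illustration on assumed prevalences. Take seven sites of equal size, with prevalence *p_i* of EPDS ≥13 at site *i*, and score each participant only by the prevalence at her site. Counting ties as one half,

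AUC = Σ_i p_i × [Σ_{j: p_j < p_i} (1 − p_j) + ½ Σ_{j: p_j = p_i} (1 − p_j)] / [Σ p_i × Σ (1 − p_i)]

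- *All sites equal:* every pair is tied, so AUC = 0.50.
- *15, 17, 19, 20, 21, 23, 25%:* the numerator terms are 0.06375 + 0.21505 + 0.39615 + 0.57800 + 0.77385 + 1.02695 + 1.30625 = 4.360. The denominator is 1.40 × 5.60 = 7.840. AUC = 0.556.
- *10, 15, 20, 20, 25, 30, 35%:* the numerator terms are 0.04500 + 0.19875 + 0.51000 + 0.51000 + 0.93125 + 1.33500 + 1.79375 = 5.32375. The denominator is 1.55 × 5.45 = 8.4475. AUC = 0.630.

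Scored within a site, the same rule gives every participant the same value, so its AUC is 0.50 by construction. It also has nothing to offer for a country absent from training.

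These values assume that the features identify the site perfectly. Language cannot separate the two Italian sites, so language alone would achieve somewhat less where those two differ in prevalence.

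**The case against.** The strongest reply is that the article neither hides the problem nor fixes a faulty analysis. It names language heterogeneity as a risk and lists it again among the study limitations, so it cannot be said to dismiss it. Two other mitigations remain. The sentence may also mean only that typing and voice signals are scored without regard to content, and the spoken and typed activities are done at leisure. The acknowledgement of risk stands. The milder reading does not rescue the sentence: verbal fluency is a scheduled language task, and content-free acoustic or keystroke features can still differ between languages.

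A reader might go further and infer that the planned cross-validation will let models score by recognising the site. The document does not support that. It does not state the splitting unit, so it fixes no wrong one, and a condensed article commonly leaves fold design, nesting and tuning to the full plan. Their absence here is no finding. Site recognition would also need prevalence that differs by site, features that identify the site and scoring pooled over sites. None of these is stated, all sites apply the same screening threshold, and in a federated setting performance might be computed within each site.

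Stroop is not used as an example of a language task, because the article says only "They will also complete the Stroop test, to measure negative attentional bias" and does not describe the stimuli.

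Making leave-one-country-out the main performance estimate would be a matter of preference, since the article does not say that generalisable means valid in unseen countries. Within-language standardisation also needs feature data from a held-out country. That is a real limit, but no outcome data are needed.

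**Conclusion.** The contradiction is certain from the text. A stated safeguard is wrong for at least three listed tasks or activities, and at least one of these, verbal fluency, falls within the named model inputs. The limitations text and the task description must be reconciled.

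The effect on the models is possible but of unknown size. In the illustration, the pooled AUC available from site alone is 0.50 under equal prevalence, about 0.56 for a 15–25% spread and about 0.63 for 10–35%. These figures rest on assumed prevalences, seven equal sites, perfect site identification and pooled scoring. They show why the point deserves an explicit analysis, not that the results will be biased. It concerns the secondary prediction objective; the primary engagement outcome is unaffected.

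**What to change.** 1. Correct or delete the sentence so that the limitations text agrees with Interaction with system, and acknowledge that active data extend beyond questionnaires.
2. Standardise the language-dependent features (verbal fluency, speech, keystroke) within language, using no outcome data, or report model results and feature rankings with and without them.
3. Keep all records of one participant in the same fold, since EPDS is used at baseline, third trimester and postpartum.
4. To support the generalisable aim, report leave-one-country-out performance, with both Italian sites held out together, and within-country performance, alongside the planned cross-validation.

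The change is one of wording and analysis specification, best settled before outcome data are examined. Because the federated data already sit by site, holding a country out is straightforward. The price is a little more analysis, and performance figures that may be lower and more variable, with only about 150 participants per centre behind each country except Italy.
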